## Intervention

First, a comprehensive assessment will first identify the underlying etiologies of frailty (e.g., physical inactivity, malnutrition, or psychological factors) to guide targeted interventions. Individualized treatment goals will be established using Goal Attainment Scaling (GAS), with subsequent implementation of personalized intervention plans. For participants presenting with ≥ 2 concurrent issues, multidisciplinary specialists will coordinate simultaneous management.

Participants identified with malnutrition or mood disorders will undergo standardized nutritional assessment (e.g., Mini Nutritional Assessment) and psychological evaluation (e.g., Geriatric Depression Scale). Evidence-based nutritional supplementation and/or pharmacotherapy will be initiated according to established clinical guidelines when indicated.

The patients of the intervention group with poor physical function would receive exercise prescription tailored to the subjects’ physical ability from a trained specialist. For Participants requiring exercise-based interventions, a moderate and gradually increasing intensity exercise regimen home-based, three times a week will be administer under telehealth-based monitoring. A standardized protocol exercise intervention comprises a 20-30-minute session with progressive phases, over a 12-week duration: 5-minute dynamic stretching warm-up, 10-minute moderate-intensity cardiovascular training, 5-minute progressive resistance exercises, 5-minute proprioceptive neuromuscular facilitation, and 10-minute isometric stance maintenance. Certified exercise specialists will individualize each prescription by modifying intensity, duration, and modality based on comprehensive geriatric assessment, while maintaining core therapeutic components to ensure safety, efficacy, and sustainable adherence.

### Formulation of intervention objectives and assessment of intervention efficacy

Intervention objectives and goal attainment will be evaluated using Goal Attainment Scaling (GAS), a standardized individualized methodology for establishing and assessing progress toward personalized objectives. The GAS process involves: (1) goal identification; (2) baseline status determination; (3) specification of outcome levels on a five-point ordinal scale (−2 to + 2); (4) goal weighting; and (5) follow-up scoring by comparing achieved outcomes with predefined attainment levels. This structured approach enables quantitative measurement of intervention efficacy across diverse clinical targets.

The research team formulated an initial pool of potential goals derived from the International Classification of Functioning, Disability, and Health (ICF) framework. Following rigorous focus group evaluations assessing goal relevance, clinical significance, and practical applicability, 25 individualized goal indicators were finalized. These indicators encompassed five key domains: body functions, mental functions, sensory functions, domestic life, and cardiopulmonary function, each tailored to meet participants’ specific needs and preferences. The complete set of 25 individualized goals is detailed in Table 1.

**Table 1 Tab1:** Goals pool for individualized interventions on frailty elderly

Domain	Area	Category
Body functions	1.1 Mental functions	1.1.1 Orientation functions
		1.1.2 Energy and drive functions
		1.1.3 Sleep functions
		1.1.4 Attention functions
		1.1.5 Memory functions
		1.1.6 Emotional functions
	1.2 Sensory functions and pain	1.2.1 Proprioceptive function
		1.2.2 Sensation of pain
	1.3 Organic functions	1.3.1 Voice functions
		1.3.2 Heart functions
		1.3.3 Blood vessel functions
		1.3.4 Blood pressure functions
		1.3.5 Hematological system functions
		1.3.6 Respiration functions
		1.3.7 Ingestion functions
		1.3.8 Defecation functions
		1.3.9 Weight maintenance functions
		1.3.10 Water, mineral and electrolyte balance functions
Activity	2.1 Mobility	2.1.1 Exercise tolerance functions
		2.1.2 Mobility of joint functions
		2.1.3 Muscle power functions
		2.1.4 Control of voluntary movement functions
	2.2 Sensations of Mobility	2.2.1 Sensations related to muscles and movement functions
		2.2.2 Sensations associated with cardiovascular and respiratory functions
Environmental factors	3.1 Support and relationships	3.1.1 Family life functions

Through a structured collaborative process involving physicians, participants, and caregivers, each individual will select three personalized goals. Under the research team’s guidance, participants will actively engage in both goal-setting and baseline evaluations, assessing each goal’s importance and anticipated difficulty on a 0–3 scale. These ratings will be multiplied to generate a weighted goal score. Outcome measurement will employ a 5-point scale (−2 to + 2) where − 2 indicates much worse than expected, −1 somewhat worse, 0 expected achievement, + 1 somewhat better, and + 2 much better than expected outcomes. This standardized approach ensures systematic evaluation while maintaining individualization of therapeutic objectives.

Goal Attainment Scaling (GAS) scores were calculated using a standardized formula and evaluated at baseline, 3-month, and 12-month follow-ups. An aggregated T score with a mean of 50 and an SD of 10 was obtained. T is the composite score, wi is the weight assigned to the ith goal, xi is the numerical value (− 2 to + 2) of the attainment level of the ith goal. The extent to which goals are achieved is standardised into a T score by the formula:$$\:GAS\:score=\:50\:+\:\:\:\:\frac{[10\sum\:\left(\text{w}\text{i}\times\:\text{x}\text{i}\right)]}{\surd\:[0.7\sum\:{wi}^{2}+{0.3\left(\sum\:wi\right)}^{2}]}$$

### Outcomes

The primary outcome measure was Goal Attainment Scaling (GAS) score, which quantitatively assessed individualized goal achievement. The secondary outcome is the reversal rate of frailty, defined as a reversion from frailty to pre-frailty or non-frailty.

### Statistical analysis

Outcome measures will be reported descriptively with 95% CIs. The GAS score and the reversal rate of frailty will be estimated between the intervention group and the control group. Responsiveness to the combined resistance band exercise and nutritional support intervention may exhibit significant variation across different ages within our target population of adults aged ≥ 60 years. To address this and avoid overgeneralization, we plan to conduct pre-specified subgroup analyses based on the following age brackets: 60–69 years, 70–79 years, and ≥ 80 years. These analyses will explore potential differences in intervention effectiveness thereby providing a more nuanced understanding of outcomes across the older adult spectrum. SPSS software (V.25, IBM Corp) will be used for statistical analysis.

### Adverse events

Potential adverse events (AEs) may include musculoskeletal pain, falls, nocturnal leg cramps and orthostatic hypotension. We will meticulously document all AEs and manage them appropriately. Participants who experience AEs will receive timely clinical assessment and appropriate medical care. All AEs will be discussed with the chief investigator who will assess seriousness and causality. AEs will also be reported to the study sponsor. Furthermore, all Suspected Unexpected Serious Adverse Reactions (SUSARs) will be reported to the ethics committee. SUSARs are defined as any episode during the study period that requires inpatient hospitalization, results in persistent/significant disability, is life threatening or results in death. The trial will be stopped prematurely if three or more SUSARs occur.

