### Inclusion and exclusion criteria

The inclusion criteria were the following: (1) ≥ 60-years old; (2) recognized as frailty by Fried scale.

The exclusion criteria were the following: (1) considered with life expectancy <1 year such as advanced cancer patients; (2) difficult to communicate with such as patients with severe cognitive impairment (Mini Mental State Examination score ≤ 17); (3) severe hearing discord.

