### Randomization

Once a patient fulfills the criteria, after informed consent, participants will be randomly assigned to either the Usual care group or the Intervention group based on random number at a 1:1 ratio generated in a blinded manner by the computerized randomization system. The information of random group allocation will be maintained in a sealed envelope opened only by a trial manager who is not involved in the recruitment, assessment, or intervention to assign the treatment. The control group will receive routine diagnosis and treatment, while the intervention group will receive individualized interventions.

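### The SUSAR definition uses seriousness alone, and a mandatory stop at three events rests on it without using the causality assessment

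*Protocol article*

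**What the plan says.** Everything at issue stands in the Adverse events section of the protocol article.

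- Assessment: "All AEs will be discussed with the chief investigator who will assess seriousness and causality".
- Reporting: "Furthermore, all Suspected Unexpected Serious Adverse Reactions (SUSARs) will be reported to the ethics committee".
- Definition: "SUSARs are defined as any episode during the study period that requires inpatient hospitalization". The sentence goes on to list lasting or marked disability, threat to life, and death.
- Stop: "The trial will be stopped prematurely if three or more SUSARs occur".

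The section also gives examples of anticipated events: "Potential adverse events (AEs) may include musculoskeletal pain, falls, nocturnal leg cramps and orthostatic hypotension". It does not link that list to the definition or to the stop.

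Elsewhere, the article sets 80 participants per group, 160 in all, with 20% attrition allowed for (Justification of sample size), and follow-up at 3 and 12 months. The Background and Discussion both say that frailty raises the risk of hospital admission and death.

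**The concern.** The term has three working parts besides "adverse": the event is serious, it is suspected to be a reaction to something done in the trial, and it is unexpected. The printed definition keeps the first and drops the other two. This would be a slip of terminology if nothing depended on it, but a mandatory stop does.

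Under the printed definition an admission for an unrelated illness counts the same as an injury caused by the exercise programme. It counts in either arm, and three admissions of a single participant would be enough. Under the ordinary meaning of the name, none of those unrelated admissions would count. When a third admission occurs, staff who follow the definition must stop the trial, and staff who follow the name need not.

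The eligibility criteria do little to keep such events rare. The closest is the exclusion of people "considered with life expectancy <1 year such as advanced cancer patients". No criterion removes people who are likely to be admitted to hospital for other reasons. What is at stake is an unneeded termination, or a dispute over whether termination is required.

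**Working it through.** **Elements of the term against the text**

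| Element | In the name | In the definition | In the stop sentence |
|---|---|---|---|
| Serious | yes | yes | through the definition |
| Suspected to be a reaction | yes | no | no |
| Unexpected | yes | no | no |
| Limited by arm | not stated | no | no |

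Causality is assessed for all adverse events. The result has no stated role in the last two columns.

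**The number at risk.** The threshold of three is a rule without a derivation, so there is no figure to reproduce. The sample size it applies to does reproduce: 64 / (1 − 0.20) = 80 per group, and 2 × 80 = 160. If the 20% lost contribute no events, 160 × 0.80 = 128 remain.

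**Chance of reaching three on the literal reading.** Let r be the risk that a participant has at least one qualifying episode in 12 months. The article does not give r, so it is an assumption and a range is shown. With independent participants, X ~ Binomial(n, r) and

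P(X ≥ 3) = 1 − (1−r)^n − n·r·(1−r)^(n−1) − [n(n−1)/2]·r²·(1−r)^(n−2).

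Example with n = 160, r = 0.02: the three terms are 0.03946, 160 × 0.02 × 0.98^159 = 0.12885, and 12,720 × 0.0004 × 0.98^158 = 0.20906. They sum to 0.37737, so P = 1 − 0.37737 = 0.6226.

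| Assumed r | Expected affected of 160 | P(3 or more), n = 160 | P(3 or more), n = 128 |
|---|---|---|---|
| 0.5% | 0.8 | 4.7% | 2.7% |
| 1% | 1.6 | 21.6% | 13.7% |
| 2% | 3.2 | 62.3% | 47.3% |
| 3% | 4.8 | 86.1% | 74.2% |
| 5% | 8.0 | 98.8% | 95.7% |

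A stop becomes more likely than not at r of about 1.7% with 160 followed, and about 2.1% with 128. With 160 it reaches 95% at r of about 3.9%. The calculation counts affected participants, whereas the rule counts events, so repeat episodes would raise these probabilities.

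**How far the two readings differ.** Take r = 5% and suppose a share s of affected participants had an event that was both related and unexpected (s is also an assumption). The risk that counts is then 0.05 × s. With n = 160:

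- s = 2%: risk 0.1%, P = 0.06%
- s = 10%: risk 0.5%, P = 4.7%
- s = 20%: risk 1%, P = 21.6%

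The literal reading gives 98.8% at the same r.

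**The case against.** The strongest reply is that the name supplies suspicion and unexpectedness, the sentence only spells out what serious means, and the causality assessment is there to sort the events. On that view this is loose drafting in a condensed article, and the probabilities for the literal reading do not apply. Part of this stands. Related and unrelated events are separated when they are assessed, so a reader who infers that the plan never separates them goes too far. But the sentence is worded as a definition and covers any episode. A label does not override an explicit definition, and the stop sentence never calls on the causality result. Nor is this detail left to a fuller document, because both the definition and the rule are printed.

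A second reply is that the literal rule errs on the side of protecting participants. That is true. It does not hide harm, and nothing in the text suggests that it biases the comparison of outcomes. Its cost is a possible needless stop.

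Two further inferences are tempting and are not supported. One is that the trial is almost certain to stop: the article gives no event rate, and the result runs from 4.7% to 98.8% over the assumed range with 160 followed. The other is that no usual-care event could be related to the study. The Randomization section does say "The control group will receive routine diagnosis and treatment, while the intervention group will receive individualized interventions", but the Abstract has all participants set goals through GAS, and eligibility involves grip and walking tests. A usual-care participant could therefore be harmed by a study procedure, and a correction must not exclude that arm outright.

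**Conclusion.** The definition is wrong as written, and a mandatory stopping rule depends on it. That conclusion rests on the text alone. The size of the consequence rests on an assumed event rate: at 12-month risks of 1%, 2% and 5%, the literal rule would be met with probability 22%, 62% and 98.8% if 160 are followed, and 14%, 47% and 96% if 128 are. These figures assume independent participants, a 12-month study period for each, and counting across both arms. They are illustrations and do not forecast this trial. The point should be fixed because the wording could end the trial on events that have nothing to do with the intervention, and because the name and the definition give different counts for the same rule.

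**What to change.** Amend the Adverse events section in three places.

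1. Make the present list (hospital admission, disability, threat to life, death) the definition of a serious adverse event, and keep reporting every such event to the ethics committee.
2. Define a SUSAR as a serious adverse event that the chief investigator judges suspected to be related to the intervention or to a study procedure, in either arm, and that is unexpected.
3. State that the stop at three counts only events that meet this corrected definition.

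One choice should be put to the sponsor and the ethics committee: whether the stop should also count related serious events that are expected. The intervention includes an "exercise regimen home-based, three times a week will be administer under telehealth-based monitoring", and falls are on the article's own list of potential events. A serious fall during home exercise could be classed as expected and then not count. The number three is also theirs to set.

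The cost is a wording amendment. Ethics-committee reporting is not reduced. The downside is that unrelated serious events would no longer trigger an automatic stop, so the chief investigator's causality judgement would carry more weight than it does under the literal text.

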### Organization of the trial

The trial is structured with two operational units: a working group overseeing study design and a data collection group managing participant interactions. To optimize protocol compliance, each participant will be assigned a dedicated study staff member who will coordinate data collection visits, address study-related inquiries, and provide ongoing support. Regular meetings will be implemented to monitor protocol adherence, identify potential implementation barriers, and resolve operational challenges in a timely manner. This dual-level organizational framework ensures both standardized data collection procedures and individualized participant engagement throughout the study duration.

## Discussion

Global healthcare systems face escalating demands due to population aging, prompting increased focus on interventions to preserve functional capacity and maintain quality of life in older adults through targeted research initiatives and policy reforms. Approximately 1 in 6 community-dwelling older people may have frailty. Data from 120,000 adults aged 60 + from 28 countries show an incidence rate of 43.4 new cases per 1000 person-years [2, 3]. Frailty management has become an increasingly critical focus in geriatric research and clinical practice. Frailty-focused interventions have the potential not only to generate large health care savings but also to lead to important reductions in the physical, emotional, social, and financial problems attributable to disability.

Frailty is characterized by diminished physiological reserve and impaired stress response capacity, clinically manifested by reduced physical activity, sarcopenia, fatigue, and slowed gait velocity. This multisystem dysregulation predisposes to significant functional decline and elevates risks for multiple adverse outcomes including disability, institutionalization, hospitalization, and mortality. Notably, frail older adults demonstrate impaired physical function with heightened vulnerability to rapid functional deterioration and diminished quality of life. Evidence confirms frailty as both an independent predictor of surgical complications, prolonged hospital stays, accelerated deconditioning, and a robust mortality indicator, while concurrently driving substantial healthcare utilization costs [44–49]. 

Frailty is a dynamic reversible state, that can be improved or reversed [11–17]. Compared with disabled elderly people, elderly people with moderate functional limitations are expected to live longer, so improving the functional status of frail elderly people is meaningful. While no definitive gold-standard treatment exists for frailty, current evidence supports multimodal interventions including structured exercise regimens and psychosocial therapies for improving physical function. Optimal management requires a comprehensive, patient-centered approach incorporating systematic identification of individual risk factors.

The advantage of the present study is the method of intervention. The methodological strength of this study lies in its comprehensive intervention approach, which differs from conventional randomized controlled trials targeting single domains (e.g., nutrition, psychology, or physical function). By employing Goal Attainment Scaling (GAS) to establish personalized objectives, we implemented truly individualized interventions tailored to each participant’s specific clinical needs and functional priorities.

GAS is an individualized scale for setting and evaluating progress toward personalized goals, that can be feasible with older adults with multiple chronic conditions and complex needs [34–40]. A study showed that 74% of functionally impaired elderly patients with multiple chronic conditions achieving their designated goals through GAS-based interventions. GAS enhances clinical practice by facilitating patient and caregiver engagement, enabling precise identification of priority concerns, and guiding the implementation of tailored treatment strategies that address each individual’s most salient healthcare requirements.

If a positive consequence could be obtained, a novel treatment for frail elderly patients can be carried out in routine clinical practice. Nonetheless, several study limitations warrant consideration. First, the goal pool was developed through expert consultation, which may introduce selection bias and limit the generalizability of the identified goals. Second, the study was conducted exclusively in Beijing, which possesses substantially greater healthcare resources than most Chinese regions, potentially restricting the applicability of our findings to less resourced settings. Consequently, caution should be exercised when extrapolating these results to other healthcare contexts.

## Data Availability

No datasets were generated or analysed during the current study.
